### Specific aims

The CM intervention is being evaluated by comparing uptake of testing, linkage, and retention in care in 15 communities randomized to either an intervention condition (*n* = 8) or a control condition (*n* = 7) located within the Agincourt HDSS. To measure outcomes in each village, we are linking the longitudinal population-based HDSS data to a health facility-based electronic clinical tracking system used in all HDSS health facilities. The linkage of the health facility and census data allows us to establish an open cohort of approximately 34,000 18–49-year-old residents that includes exposure data (village of residence) as well as outcome data (HIV-related clinical care). Using these data, we will evaluate the effects of the CM intervention by village randomization arm as well as characterize the HIV care cascade in a high prevalence population. We will also evaluate the conceptual model, including the hypothesized CM processes [52], through community surveys to monitor intervention exposure and community level change using validated CM measures [53]. The specific aims of the study include:

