Primary analyses will follow an intent-to-treat (ITT) approach and will be unadjusted except for intervention group, and, for longitudinal analyses, time, and the group-by-time interaction. Individual will be the unit of analysis. Our principal interest is to estimate the marginal or population-average effect of the intervention on each outcome rather than the effect for a hypothetical average subject [70]. Moreover, within-subject correlations among outcomes are considered nuisance parameters rather than quantities of interest to be modeled explicitly. Accordingly, generalized estimating equations (GEE) will be used to perform the proposed primary longitudinal analyses, including planned time-averaged comparisons of post-baseline measurements across the intervention and control arms to test primary hypotheses 1–3 listed above. Alpha will be set at .05 for these planned comparisons of each separate outcome. Any additional post-hoc comparisons (e.g., paired comparisons of the control and intervention arms at each time point) will maintain a nominal alpha level of .05 through the use of simulation-based stepdown multiple comparison methods [71]. GEE accounts for correlation of repeated measurements from the same research participant via computation of a working correlation matrix and yields the desired marginal population-average effect estimates [72]. Village ID will be included as a nested fixed effect or via alternating logistic regression (ALR) to account for clustering of persons nested within villages. GEE estimates are consistent even if the correlation structure is mis-specified, though GEE’s statistical efficiency improves as the working correlation structure more closely approximates the actual correlation structure [73]. Thus, several suitable working correlation structures will be considered (e.g., unstructured, AR(1), exchangeable) [74]. The QIC or a similar statistic will be used to select the final working correlation structure [75]. Robust Huber-White “sandwich” standard errors will be used to obtain correct inferences even if the chosen correlation structure remains slightly mis-specified.

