For hypothesis 4, cross-sectional population data will be collected through representative community surveys. Summary measures of the CM domains before and after the intervention for each village will be calculated from this population representative sample. GEE will be used to model the effects of the pre-post differences in village-level CM domains on individual residents’ HIV testing, and, for HIV-positive individuals, linkage and retention to care using the same overall modeling approach as outlined above. To examine the relative importance of each of the six CM domains, initial models will include the pre-post change scores for each of the six domains in a single model. Subsequent analyses will isolate the marginal effects of each domain via G-computation or other substitution-based estimation strategy [60, 76].

Secondary analyses will extend GEE models to incorporate additional covariates of interest drawn from the HDSS data (e.g., age; gender) and examine their interactions with intervention assignment to ascertain statistical moderation. Secondary analyses will also evaluate whether the pre-intervention/post-intervention village-level difference in the six community mobilization measures mediate the relationships between intervention village residence and the primary outcomes. Statistical mediation will be assessed using the causal inference-based approach of Valeri and VanderWeele, which yields optimal estimates of indirect effects in the presence of binary outcomes and moderator-mediator interactions [77]. M*plus* will be used to implement these mediation analyses because it allows for causal mediation assessment incorporating robust standard errors to address clustering of individuals within villages [78]. Significant indirect and total effects of the intervention on testing, linkage, and retention accompanied by non-significant direct effects will signify mediation in this context.

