### Power

Minimum detectable differences were calculated according to the methods for proportions in cluster randomized trials proposed by Hayes and Moulton [54], yielding conservative effect size estimates based on clustering by villages. Based on the HDSS data, there are approximately 30,000 adults 18–49 in the study area. We assumed an HIV prevalence of 33% in the adult target population (18–49-year old) [51]. If we conservatively estimate that testing is constant at 35% of the population, at least a third of those tested each year were not tested previously in the study period, and that test positivity is 15% (again a conservative estimate), 449 cases of HIV would be newly identified each year. We further assumed that approximately 50% of individuals who present for CD4 staging would be eligible for HIV treatment under 2014 guidelines. Approximately 6000 individuals were known to be on treatment at clinics in this area in 2014. Our survey data from 2012 suggests that HIV testing in this region exhibits an intra-class correlation of 0.014. In adjustments of power calculations for clustering of outcomes by village, we conservatively assumed an intra-class correlation of 0.05. Table 3 includes outcome estimates for the control proportions based on current literature [18, 26, 27, 68, 79], and the target (intervention) proportions with the minimum increase in proportions that would be detectable as a statistically significant change at alpha of 0.05 and power of 0.80, given the above assumptions. In 2016 (1 year into data collection), the South African government announced universal HIV treatment. This should increase our sample size to assess initiating ART (aim 2) and retention in care (aim 3) in the second and third years of the study.

**Table 3 Tab3:** Power calculations–minimum detectable effects

Outcomes: proportion of population	Current estimate	Intervention group target	Minimum detectable difference (proportion)
Testing; tested in past 12 months	35%	60%	19%
Linkage; undergoing CD4 staging within 3 months of positive test	65%	85%	18%
Linkage; eligible for ART who initiate treatment within 3 months	60%	80%	19%
Retention; HIV positive who remain in care at 12 months	50%	70%	19%

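### The mediation rule requires a non-significant direct effect, so it can read partial mediation as complete and, taken literally, does not count partial mediation at all

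*Protocol article*

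**What the plan says.** The Analysis section (secondary analyses) asks whether the pre-to-post "village-level difference in the six community mobilization measures mediate the relationships between intervention village residence and the primary outcomes". It adopts a causal-inference mediation method, with software chosen for "incorporating robust standard errors to address clustering of individuals within villages". It then says how the results will be read: "Significant indirect and total effects of the intervention on testing, linkage, and retention accompanied by non-significant direct effects will signify mediation". Three conditions must therefore hold together: a significant indirect effect, a significant total effect and a non-significant direct effect.

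No equivalence margin or other interval criterion is set for the direct effect, and no power is given for it. The only precision figures are in the Power section. Table 3 gives minimum detectable differences of 18 or 19 points for each whole intervention effect, each being a "statistically significant change at alpha of 0.05 and power of 0.80", with 15 villages split 8 to 7.

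**The concern.** A non-significant test of the direct effect can mean that the effect is absent or that the trial could not see it. The rule does not separate the two. This has two consequences.

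- **Partial read as complete.** Where a real direct effect is missed, the significance pattern suggests that mobilization explains the whole effect when it explains only part.
- **Partial not recognised.** Where indirect and direct effects are both real and both significant, the pattern is not met. More precise data make this outcome more likely, which is the wrong direction for a rule about evidence.

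Partial mediation is plausible on the article's own account. The programme also works on stigma and gender norms, and Table 2 lists these as covariates, separate from the six mobilization domains used as mediators. Effects through those routes could appear as a direct effect. Mechanism is a named aim (aim 4) and features in the Conclusions, so how it is read matters, although no primary test depends on it.

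**Working it through.** **Inputs from the documents.** 15 villages, 8 against 7; alpha 0.05 (sidedness not stated, two-sided assumed); power 0.80; testing 35% in control, 60% target (25 points), minimum detectable difference 19 points; planning intra-class correlation (ICC) 0.05; ICC for testing in the 2012 survey 0.014; about 30,000 adults, so 30,000/15 = 2,000 per village.

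**Assumed, because the documents give no figure.** The direct share f of the total effect; the squared correlation R² between arm and mediator (0, 0.3, 0.5); one or six mediators per model; effects that add on the percentage-point scale.

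**The plan's own figures.** The cited cluster-trial formula with ICC 0.05, 7 villages per arm and one added cluster gives a detectable difference of 17.7 points for testing, 17.9 for retention, 19.6 (one year of diagnoses) or 17.2 (three years) for CD4 linkage, and 23.6 or 19.4 for ART initiation. Table 3 has 19, 19, 18 and 19. No variant tried returns all four. The article does not give the cluster size behind each row, so nothing is made of this here. Step 1 uses only the stated 80% and 19 points.

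**Step 1: scale the stated power.** The implied standard error is 19/(1.96 + 0.84) = 19/2.80 = 6.79 points. Check: Φ(2.80 − 1.96) = Φ(0.84) = 80%. For a total effect T with direct share f, and the same standard error for the direct effect:

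power = Φ(f × (T/19) × 2.80 − 1.96)

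| Direct share f | T = 19: power | T = 19: non-significant | T = 25: power | T = 25: non-significant |
|---|---|---|---|---|
| 25% | Φ(0.70 − 1.96) = 10% | 90% | Φ(0.92 − 1.96) = 15% | 85% |
| 50% | Φ(1.40 − 1.96) = 29% | 71% | Φ(1.84 − 1.96) = 45% | 55% |
| 75% | Φ(2.10 − 1.96) = 56% | 44% | Φ(2.76 − 1.96) = 79% | 21% |

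**Step 2: compute the standard error from the ICC (testing).** The design effect is 1 + 1,999 × ICC, which is 100.95 at ICC 0.05 and 28.99 at 0.014. With T = 19 (54% against 35%):

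SE² = design effect × [0.54 × 0.46/(8 × 2,000) + 0.35 × 0.65/(7 × 2,000)]

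This gives an SE of 5.66 points at ICC 0.05 and 3.03 at 0.014. With T = 25 the values are 5.62 and 3.01. In the table below, the low end of each range is a z-test with no variance inflation. The high end is a t-test on 7 degrees of freedom (15 villages less intercept, arm and six mediators) with variance inflated by 1/(1 − 0.5).

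| Probability that the direct effect is non-significant | f = 25% | f = 50% | f = 75% |
|---|---|---|---|
| ICC 0.05, T = 19 | 87–92% | 61–82% | 29–66% |
| ICC 0.05, T = 25 | 80–89% | 40–72% | 8–47% |
| ICC 0.014, T = 19 | 65–84% | 12–52% | 0–19% |
| ICC 0.014, T = 25 | 45–75% | 1–29% | 0–4% |

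**Step 3: the effect of precision.** Take T = 25 with half direct, so 12.5 points. On the z-test without inflation, an SE of 5.62 leaves the direct effect non-significant with probability 1 − Φ(12.5/5.62 − 1.96) = 1 − Φ(0.26) = 40%. An SE of 3.01 leaves 1 − Φ(4.15 − 1.96) = 1 − Φ(2.19) = 1%. The causal structure is the same, but with better data the pattern is almost never met.

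**Step 4: the whole three-part rule.** In a 15-village simulation at ICC 0.05 with a 19-point total, half direct, and assumed mediator settings, the direct effect was non-significant in 68–92% of the trials in which total and indirect effects were significant. With no mediation at all (the whole effect direct), the rule declared mediation in about 0–3% of trials.

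**The case against.** **False declarations are guarded against.** A reader might infer that the rule declares mediation whenever the direct effect is non-significant, and so largely from noise. The text does not support that. The indirect and total effects must also be significant, and in simulation the full rule declared mediation where there was none in only about 0–3% of trials. This objection stands and limits the point to partial mediation.

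**The size depends on the scenario.** A reader might also take non-significance to be the likely result whether or not a direct effect exists, or take 71% as a floor. Neither holds. The article calls the ICC of 0.05 conservative. At 0.014, a half-direct effect on testing would more often than not be found in nearly all settings tried. Robust standard errors without a small-sample correction, which the article does not mention, reduce non-significance to 43–67% in the simulated 19-point, half-direct case. A mediator that explains differences between villages could also sharpen the direct estimate. This stands too. However, a direct share of a quarter is still missed 45–84% of the time at ICC 0.014.

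**The sentence may not be exclusive.** It says what will signify mediation, not that nothing else will. That is fair, but no other pattern is offered, so the literal reading leaves partial mediation out.

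**The six-domain model is a separate matter.** A reader might extend the criticism to the hypothesis 4 plan, where "initial models will include the pre-post change scores for each of the six domains in a single model". That model serves to compare the domains, is described as a starting point, and is followed by estimation of each domain's marginal effect. The article does not say how many mediators enter each mediation model. Replacing the joint model would be a debatable trade-off, and it is not requested here.

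**Conclusion.** The point holds for the non-significance condition alone. It treats failure to detect a direct effect as its absence, and read literally it gives partial mediation no place. The likely errors are calling mediation complete when it is partial and failing to recognise partial mediation; inventing mediation is not among them.

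At the article's stated precision, a direct effect of up to about half the total would be missed more often than found: 71% of the time at a 19-point total and 55% at 25 points. A direct effect of three quarters of the total would more often be found (44% and 21% missed). These figures rest on an assumed direct share, a two-sided 5% test, additive effects in percentage points, and a direct-effect standard error equal to that of the total effect. For testing at ICC 0.014 the rates fall, but the logical fault does not depend on them. At low precision the condition misreads the direct effect, and at high precision it excludes partial mediation.

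The consequence is confined to a secondary analysis bearing on aim 4. Primary hypotheses 1–3 are unaffected.

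**What to change.** - Delete the requirement that the direct effect be non-significant.
- Base the mediation conclusion on the natural indirect effect with a 95% interval that reflects 15 villages, not the number of individual records.
- Report the direct effect and the proportion mediated, each with its interval.
- State that partial mediation counts as mediation.

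The planned causal mediation method is already aimed at indirect effects, so this is a small change to a secondary analysis: the decision sentence, plus intervals with village-level uncertainty. The price is that complete mediation can no longer be concluded from a non-significant direct effect alone.

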### Power

Minimum detectable differences were calculated according to the methods for proportions in cluster randomized trials proposed by Hayes and Moulton [54], yielding conservative effect size estimates based on clustering by villages. Based on the HDSS data, there are approximately 30,000 adults 18–49 in the study area. We assumed an HIV prevalence of 33% in the adult target population (18–49-year old) [51]. If we conservatively estimate that testing is constant at 35% of the population, at least a third of those tested each year were not tested previously in the study period, and that test positivity is 15% (again a conservative estimate), 449 cases of HIV would be newly identified each year. We further assumed that approximately 50% of individuals who present for CD4 staging would be eligible for HIV treatment under 2014 guidelines. Approximately 6000 individuals were known to be on treatment at clinics in this area in 2014. Our survey data from 2012 suggests that HIV testing in this region exhibits an intra-class correlation of 0.014. In adjustments of power calculations for clustering of outcomes by village, we conservatively assumed an intra-class correlation of 0.05. Table 3 includes outcome estimates for the control proportions based on current literature [18, 26, 27, 68, 79], and the target (intervention) proportions with the minimum increase in proportions that would be detectable as a statistically significant change at alpha of 0.05 and power of 0.80, given the above assumptions. In 2016 (1 year into data collection), the South African government announced universal HIV treatment. This should increase our sample size to assess initiating ART (aim 2) and retention in care (aim 3) in the second and third years of the study.

**Table 3 Tab3:** Power calculations–minimum detectable effects

Outcomes: proportion of population	Current estimate	Intervention group target	Minimum detectable difference (proportion)
Testing; tested in past 12 months	35%	60%	19%
Linkage; undergoing CD4 staging within 3 months of positive test	65%	85%	18%
Linkage; eligible for ART who initiate treatment within 3 months	60%	80%	19%
Retention; HIV positive who remain in care at 12 months	50%	70%	19%

## Discussion

The Tsima ra rihanyu program is built on a theory-based CM model that aims to remove the major social barriers to successful participation in the HIV care cascade and ultimately activate the promise of TasP. The cluster-randomized research design and the linked data sources including a measure of CM administered through community surveys will provide a robust structure within which to evaluate the intervention and simultaneously, provide insight as to the mechanisms of action in improving testing, linkage, and retention. In addition, because the study is embedded in an HDSS, we will have true denominators for our estimates and will therefore generate much needed population-based data contributing to improved characterization of the HIV care cascade. These data will also provide an opportunity to optimize program design through targeting groups with the greatest need of care support.

This study focuses on community approaches to improving uptake of HIV testing and care and is not focused on directly mitigating health facility-level barriers to care, including quality of HIV care, drug stock-outs, long wait times, or lack of confidentiality. However, the intervention design does not prohibit mobilization teams and/or CATs to plan activities at the clinics or with the clinics and does encourage partnerships with clinic leadership as primary stakeholders in improving the care cascade. Because intervention and control populations will be accessing the same group of clinics and because varied quality of care across the health facilities and different levels of involvement in the intervention by health facility could affect the study outcomes, the team agreed that any intervention activities that target health facility leadership or address health facility services will be conducted in all study health facilities, in order to ensure that potential effects of clinic-based activities will be consistent across all villages. Additionally, to address basic health facility functionality, and mitigate any health facility-specific influence on study outcomes, the team has partnered with the local PEPFAR partner, Right to Care, to work with all study area health facilities to ensure that best practices for HIV prevention, testing, care, and treatment are in place and that monitoring systems and data capture are standardized and that supplies, including test kits and drugs, are available.

The Tsima ra rihanyu program is also rooted in community collaboration and feedback, with community participation in setting goals as well as monitoring progress towards reaching those goals. A key strength of this intervention is the ability to assess the care cascade in each community over time. In the first year of the intervention, we held goal-setting workshops with each intervention community to establish commitment and partnership towards improving HIV outcomes in the community. The concept of the UNAIDS 90-90-90 goals was introduced during these meetings and community leaders, and participants were able to both assess the current state of HIV testing and care outcomes in their community and establish annual community goals. Every 6 months, the team will hold a similar community meeting to monitor achievements towards reaching the goals and renew commitment and partnerships. Clinics are also receiving feedback on a regular basis, with a team discussion regarding where attrition is occurring in order for clinics to focus their efforts in improving clinical outcomes for their clients.

The study does have some limitations. The Tsima ra rihanyu program excludes use of mass media or large-scale public advocacy in order to minimize contamination in the context of an RCT. This omission will likely detract from the reach and impact of the intervention. Additionally, given substantial migration in the area, it is likely that some residents will be classified as lost to follow-up or out of care when they may have moved out of the area and remained in care. While information regarding changes in residency status (migration) and deaths are updated annually in the census and will be noted in the data, some residents captured in the electronic health facility data system may not present for return visits with no recorded reason for loss to follow-up. To remedy this, among those classified as lost, we will select a random sample of 10% to contact in order to determine their outcome, including whether they are seeking care elsewhere. This data will allow us to perform sensitivity analyses [80]. Additionally, we do not have current data on HIV status of all individuals in the community; therefore, the true number of residents living with HIV is unknown. We can, however, estimate the number based on previous population-based surveys in the area.

